#### Incidence density of diarrhea in terms of child-weeks

The expected value of the incidence density, E (*s*^2^), is given by$$ \mathrm{E}\left({\mathrm{s}}^2\right) = \lambda \mathrm{A}\mathrm{v}\left(1/{\mathrm{y}}_{\mathrm{j}}\right) + {\sigma^2}_{\mathrm{c}}=\lambda \mathrm{A}\mathrm{v}\left(1/{\mathrm{y}}_{\mathrm{j}}\right) + {\mathrm{k}}^2{\lambda}^2, $$

where λ is the true mean rate, *y*_*j*_ corresponds to the child-weeks of follow-up in the *j*^th^ cluster, Av() indicates the mean overall clusters, *σ*_*c*_^2^ is the between-cluster variance of the true rates, and *k* is the coefficient of variation of those rates [17]. Based on the preliminary survey, the overall diarrheal rate in the 48 *gotts* was 0.18 (or 18 cases per 100 child-weeks). The empirical standard deviation of the observed diarrhea rates was 0.092189, and the average of the reciprocal child-weeks per neighborhood was 0.001667. Therefore, *k* was estimated as$$ \begin{array}{c}\hfill {\sigma}^2={0.092189}^2-0.18\times 0.001667=0.008199,\hfill \\ {}\hfill \hfill \\ {}\hfill \mathrm{and}\;\mathrm{therefore},\;k=\surd \left(0.008199/0.18\right)=0.213422.\hfill \end{array} $$

We assumed that the diarrhea rate in the control *gotts* remained constant at λ_0_ = 0.18, and we required 90 % power (*z*_*β*_ = 1.28) if the intervention reduced the diarrhea rate by 21 %. Assuming 600 child-weeks of observation (24 weeks of follow-up for 25 children) in each *gott*, the number of neighborhoods required for each treatment group is given by c = 1 + (1.96 + 0.28)^2^[(0.18 + 0.1422)/600 + 0. 213422^2^(0. 18^2^ + 0. 1422^2^)]/(0.18 − 0.1422)^2^ = 22.55.

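### The incidence sample size uses a miscalculated coefficient of variation (0.213 instead of 0.503 on the protocol's own figures), so the stated 90 % power becomes about 34 %

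*Protocol article*

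**What the plan says.** The calculation is in the protocol article under Sample size calculation, subsection on incidence density in child-weeks. It decomposes the expected variance of observed gott rates into a Poisson part, λ·Av(1/y_j), and a between-gott part written both as σ_c² and as k²λ². It states that "k* is the coefficient of variation of those rates".

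The inputs are attributed to the preliminary survey: "the overall diarrheal rate in the 48 *gotts* was 0.18 (or 18 cases per 100 child-weeks"), followed by "The empirical standard deviation of the observed diarrhea rates was 0.092189, and the average of the reciprocal child-weeks per neighborhood was 0.001667". Subtracting the Poisson part gives σ² = 0.008199. The protocol then takes k as the square root of "0.008199/0.18", which is 0.213422.

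This k enters the sample size formula with 90 % power (z_β given as 1.28), a 21 % reduction from 0.18 to 0.1422, and 600 child-weeks per gott (24 weeks for 25 children). The printed formula begins "the number of neighborhoods required for each treatment group is given by c = 1 + (1.96 + 0.28" and its result is 22.55 gotts per arm. Under CLTS implementation, 24 of the 48 gotts form the intervention arm.

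**The concern.** The formula used to compute k contradicts the definition given just above it. If σ_c² = k²λ², then k = σ_c/λ. Taking √(σ_c²/λ) gives a quantity that is not a coefficient of variation. When its square is multiplied by λ0² + λ1² in the sample size formula, the between-gott variance is understated by a factor of 1/0.18, or about 5.6.

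The printed inputs already show the mismatch: the observed standard deviation is 0.092189/0.18 = 51 % of the mean rate, and the Poisson correction removes very little of it. A k of 0.213 would correspond to an observed standard deviation of about 0.042.

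Two smaller problems sit in the same paragraph. The value 0.001667 is the reciprocal of the planned 600 child-weeks, yet it is used to remove sampling noise from preliminary-survey rates. The formula also prints 0.28 where 1.28 is meant.

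What is at stake is the 90 % power claim for incidence. The Discussion says the trial will give sound evidence on incidence density alongside prevalence and duration. If power is really near one third, a null incidence result says little about whether a 21 % reduction exists, and a reader relying on the stated 90 % could take it as evidence against one.

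**Working it through.** **Inputs (all from the incidence-density subsection, except the number of gotts, which is from CLTS implementation)**

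- λ0 = 0.18; λ1 = 0.18 × 0.79 = 0.1422; difference 0.0378, squared 0.00142884
- Standard deviation of observed rates 0.092189; Av(1/y) = 0.001667
- y = 600 child-weeks per gott; z_α = 1.96; z_β = 1.28
- 24 gotts per arm

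**Step 1. Between-gott variance**

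σ_c² = 0.092189² − 0.18 × 0.001667 = 0.0084988 − 0.0003001 = 0.0081988. This matches the protocol.

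**Step 2. Coefficient of variation**

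- As computed in the protocol: √(0.0081988/0.18) = 0.2134
- As defined in the protocol: √0.0081988/0.18 = 0.5030

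**Step 3. Gotts per arm**

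c = 1 + (z_α + z_β)² × V, where V = [(λ0 + λ1)/y + k²(λ0² + λ1²)]/(λ0 − λ1)².

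Common terms: (0.18 + 0.1422)/600 = 0.000537 and 0.18² + 0.1422² = 0.052621.

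- Protocol's k: V = (0.000537 + 0.045549 × 0.052621)/0.00142884 = 2.053. With 3.24², c = 22.55, the printed figure.
- Protocol's k with the printed 0.28: 2.24² × 2.053 + 1 = 11.3. So 1.28 was used and 0.28 is a misprint that does not affect 22.55.
- Corrected k: V = (0.000537 + 0.25305 × 0.052621)/0.00142884 = 9.695. With 3.24², c = 102.8. For 80 % power (2.80²), c = 77.0.

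**Step 4. Power with 24 gotts per arm**

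Power = Φ(√((24 − 1)/V) − 1.96).

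- k = 0.2134: Φ(3.347 − 1.96) = 91.7 %
- k = 0.503: Φ(1.540 − 1.96) = 33.7 %

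Variants with k = 0.503:

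- without the +1: 35.0 %
- noncentral t on 46 degrees of freedom: 33.7 %
- 52 weeks of follow-up instead of 24: 34.3 %
- the same absolute between-gott variance in both arms: 28.5 %
- simulation with gamma-distributed gott rates and a t-test on gott rates: 33.9 %

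**Step 5. Detectable reduction with k = 0.503 and 24 gotts per arm**

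Solving the step 3 formula for λ1 gives about 36 % at 80 % power and about 40 % at 90 % power, against the 21 % assumed.

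**Step 6. Sensitivity to Av(1/y)**

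0.001667 is 1/600 to the digits printed. The preliminary survey's own child-weeks per gott are not given, so the values below are assumptions.

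| Survey child-weeks per gott (assumed) | σ_c² = 0.0084988 − 0.18/y | k = σ_c/0.18 | Power, 24 per arm |
|---|---|---|---|
| 25 | 0.00130 | 0.20 | 94 % |
| 50 | 0.00490 | 0.39 | 50 % |
| 100 | 0.00670 | 0.45 | 40 % |
| 600 (as printed) | 0.00820 | 0.50 | 34 % |

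Power reaches 90 % only if the survey had about 26 child-weeks per gott or fewer.

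**The case against.** The arithmetic error in k is hard to dispute; the stronger objections concern how much follows from it.

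First, 34 % depends on an input that is itself in doubt. If 0.001667 is the planned rather than the surveyed follow-up, 0.503 is not a valid estimate of k either. A single seven-day recall of 25 children per gott would supply 25 child-weeks, which gives k of about 0.20 and power of about 94 %. The 90 % claim would then be roughly right by accident. This stands as a limit on the figure: the true power cannot be determined from the document. It does not restore the claim, because the protocol does not state that input and its calculation does not use it. The origin of 0.001667 is best put as a question to the sponsor.

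Second, incidence is not the primary endpoint. Seven-day prevalence is, with its own calculation leading to 48 gotts. That is correct, and nothing here alters the primary endpoint's stated power. The protocol nevertheless makes a formal power claim for incidence.

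Third, gotts were stratified by kebelle, and an analysis using the strata would depend on the within-kebelle k, which may be smaller. This is a fair caveat, but the protocol uses an unmatched formula, takes no credit for stratification and gives no within-stratum k.

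Fourth, 0.28 is only a misprint, since 1.28 is stated just before it. Agreed: it makes the printed equation false but has no effect on the result.

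**Conclusion.** The point holds. By the protocol's own definition and figures, k is 0.503, not 0.213. The requirement for 90 % power is then about 103 gotts per arm instead of 22.55, some 4.6 times as many (102.8/22.55). The planned 24 per arm give about 34 % power for a 21 % reduction.

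The 34 % assumes the printed standard deviation, the printed Av(1/y), a common coefficient of variation in both arms, and an unmatched comparison. The other analytic variants keep it between about 28 % and 35 %. Replacing Av(1/y) could move it much further, from 40 % at 100 survey child-weeks per gott to 94 % at 25. The firm conclusion is therefore that the 90 % claim is unsupported as written and has to be re-derived; 34 % is what the printed inputs deliver. The correction must be made, although it concerns a non-primary endpoint.

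**What to change.** Rewrite the incidence-density paragraph as follows.

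1. State the preliminary survey's actual child-weeks per gott, or confirm that 0.001667 comes from that survey, and recompute σ_c² with its Av(1/y).
2. Set k = σ_c/λ.
3. Print 1.28 in place of 0.28 in the formula.
4. Restate power for a 21 % reduction, or the detectable reduction at a stated power, for the fixed 24 gotts per arm. Any credit for kebelle stratification needs a within-kebelle k with its source.
5. If k stays near 0.5, withdraw the 90 % claim and report about 34 % power for a 21 % reduction, with a detectable reduction of about 36 % at 80 % power or 40 % at 90 %.

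The cost is one corrected paragraph and possibly a less favourable stated power. The number of gotts and children does not change.

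### The incidence sample size divides the between-gott variance by the mean rate instead of its square: on the printed inputs k is 0.503, not 0.213, and 24 gotts per arm give about 34 % power, not 90 %

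*Protocol article*

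**What the plan says.** All of this is in the protocol article, under Sample size calculation, Incidence density of diarrhea in terms of child-weeks.

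- **Model.** The expected variance of the observed gott rates is λ·Av(1/y) + σ²c, and σ²c is rewritten as k²λ². The text says that k "is the coefficient of variation of those rates".
- **Survey inputs.** The overall rate is 0.18 per child-week. The spread of the gott rates is given as follows: "The empirical standard deviation of the observed diarrhea rates was 0.092189". The mean of 1/y over gotts is put at 0.001667. The between-gott variance follows as 0.008199.
- **The step at issue.** "k=\surd \left(0.008199/0.18\right)=0.213422".
- **Target.** "we required 90 % power" (with zβ given as 1.28) for a 21 % reduction, that is from 0.18 to 0.1422, with 600 child-weeks per gott.
- **Result.** 22.55 gotts per arm, from an expression that prints the z-values as 1.96 + 0.28.

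The CLTS implementation section assigns 24 of the 48 gotts to the intervention arm, so there are 24 per arm.

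**The concern.** If σ²c = k²λ², then k = σc/λ. The protocol computes σc/√λ instead. That is not a coefficient of variation, and because λ is below 1 it is too small, here by a factor of √0.18 = 0.424. The value is then squared and multiplied by (λ0² + λ1²) in the cluster formula, which is valid only for a true coefficient of variation. Between-gott variation dominates this formula, so nearly the whole error passes into the number of gotts.

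At stake is how the incidence result will be read. The protocol attaches a formal 90 % power statement to this outcome, and its Discussion promises sound evidence on incidence density. Readers who trust that statement could take a null incidence result as evidence against a 21 % reduction, when on the protocol's own inputs the trial would have had about one chance in three of detecting it.

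**Working it through.** **Inputs** (all from the incidence section, except the 24 gotts per arm): λ0 = 0.18; λ1 = 0.18 × 0.79 = 0.1422; SD of observed rates 0.092189; Av(1/y) = 0.001667; y = 600 child-weeks per gott; z = 1.96 and 1.28.

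**1. Between-gott variance.** 0.092189² − 0.18 × 0.001667 = 0.008199. The printed value reproduces.

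**2. k.**
- As printed: √(0.008199/0.18) = 0.2134.
- By the protocol's definition: √0.008199/0.18 = 0.503.

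**3. Internal check.** With the printed k, k²λ² = 0.213422² × 0.18² = 0.00148, not the 0.008199 derived one line before. The implied SD of observed rates is √(0.18 × 0.001667 + 0.00148) = 0.042, against the reported 0.092.

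**4. Gotts per arm.** The protocol's formula is

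c = 1 + (z₁ + z₂)² × [(λ0 + λ1)/y + k²(λ0² + λ1²)] / (λ0 − λ1)²

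with (λ0 + λ1)/y = 0.3222/600 = 0.000537, λ0² + λ1² = 0.05262, (λ0 − λ1)² = 0.0378² = 0.001429 and (1.96 + 1.28)² = 10.498.

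- k = 0.2134: bracket = 0.000537 + 0.002397 = 0.002934, so c = 1 + 10.498 × 0.002934/0.001429 = **22.55**. The printed figure reproduces, so the wrong k was the one used.
- k = 0.2134 with the printed 0.28: c = 11.30. The 0.28 is therefore a misprint for 1.28 and did not affect 22.55.
- k = 0.503: bracket = 0.000537 + 0.013316 = 0.013853, so c = **102.8**. For 80 % power (0.84 in place of 1.28), c = 77.0.

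**5. Power at 24 per arm.** Inverting the same formula with k = 0.503: z = √[(24 − 1) × 0.001429/0.013853] = 1.540, so power = Φ(1.540 − 1.96) = **0.337**. A noncentral t on 46 degrees of freedom also gives 33.7 %. With the printed k the formula gives 91.7 %.

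**6. Detectable reduction at 24 per arm, k = 0.503.** Solving c = 24 for λ1 gives about 36 % at 80 % power and 40 % at 90 % power.

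**7. Longer follow-up.** The sanitation calendar runs for 12 months. With 52 × 25 = 1300 child-weeks per gott, power is 34.3 % and c is 100.7. More weeks do not help, because between-gott variance dominates.

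**8. Sensitivity to the subtracted sampling term.** The printed 0.001667 equals 1/600, the planned trial follow-up, and the protocol gives no other figure for the survey's child-weeks per gott. The values below are assumptions; k is computed correctly in each row.

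| Survey child-weeks per gott (assumed) | k | Power at 24 per arm |
|---|---|---|
| 600 (as printed) | 0.50 | 34 % |
| 100 | 0.45 | 40 % |
| 50 | 0.39 | 50 % |
| 30 | 0.28 | 76 % |
| 25 | 0.20 | 94 % |

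**The case against.** The formula error cannot be defended; the dispute is over its size and weight.

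- **The 34 % depends on the 1/600 term.** The sampling term should reflect the survey's own exposure, and 1/600 coincides with the planned trial follow-up. Smaller survey exposure lowers k, and at about 25 child-weeks per gott the 90 % claim would survive. With no sampling term at all, k = 0.092189/0.18 = 0.512, so 34 % lies near the bottom of the possible range. This stands as a caveat on the power figure. It does not rescue the calculation: the protocol presents 0.001667 as the survey value, and no choice of child-weeks justifies dividing by λ.
- **The prevalence section points to a smaller k.** It states a coefficient of variation of 0.15. Its design effect of 2.14 with 25 children per gott implies an intracluster correlation of 1.14/24 = 0.0475, or k = √(0.0475 × 0.76/0.24) = 0.39 at 24 % prevalence. Used in the incidence formula, these give about 99 % and 50 % power. They concern another outcome and disagree with each other, so they do not replace the k derived from the rates.
- **Randomization is stratified by kebelle.** A stratified analysis could remove part of the between-gott variance. This is true in principle, but the protocol gives no within-kebelle variance and its formula is unstratified.
- **Incidence is not the primary endpoint.** This is correct. Prevalence is primary, and its section derives 48 gotts separately. That limits the consequence, but the 90 % power stated for incidence is still unsupported.

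**Conclusion.** The error is certain and can be shown from the incidence section alone: the k used contradicts the variance equation printed above it. On the printed inputs k is 0.503, the requirement is 102.8 gotts per arm (more than four times the printed 22.55), and 24 per arm give about 34 % power for a 21 % reduction.

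The exact power is less certain than the error. It assumes the printed SD and sampling term, the protocol's unstratified formula and 600 child-weeks per gott. Of these, the survey child-weeks matter most: over assumed values from 600 down to 30, power runs from 34 % to 76 %, and it passes 90 % only near 25. The 90 % statement must be corrected. The sample size for the primary prevalence endpoint is not affected.

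**What to change.** In the incidence density paragraph:

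1. Replace the k line with k = √0.008199/0.18 = 0.503.
2. Correct 0.28 to 1.28 in the expression for c.
3. Recompute c (102.8 per arm on these inputs) and withdraw the claim of 90 % power.
4. Keep 48 gotts. State that with these inputs incidence has about 34 % power for a 21 % reduction, and give the detectable reduction, about 36 % at 80 % power, as the statement of precision.
5. State the survey's actual child-weeks per gott behind 0.001667. If they were not 600, recompute the variance, k, c and power from the true figure. Until it is known, show the power as a range.

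The cost is one corrected paragraph. The number of gotts, the number of children and the conduct of the trial do not change; the stated power for incidence becomes less favourable.

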### Household sampling methods

A list of households with children under 5 years of age was established by four supervisors in each *gott* before the baseline survey. Supervisors required 8 days to produce a complete household list for all 48 *gotts*. Using SPSS 21 Statistics software, the survey team leader randomly sampled 25 households from each *gott*. Enumerators will recruit the youngest child under five from each household, from the fifth week of October through the second week of November 2015. If the mother or a household caregiver is absent at the time of the recruitment visit, the enumerator will revisit the same household two more times. If the mother or caregiver refused to be registered, a neighboring household with a child under 5 was visited to replace the household (Fig. 3).

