### CLTS implementation

In accordance with the Ethiopian government’s guidelines on this issue, the primary approach for implementation of latrine improvement and hygiene promotion adopted for this program is Community-Led Total Sanitation. Of 48 *gotts* selected in the project area, 24 *gotts* in the project area were selected (intervention arm) and will receive the CLTS intervention and undergo intensive follow-up throughout the first phase of the implementation period (approximately 12 months) for latrine improvement. As the first step of CLTS, a team of trained CLTS facilitators will conduct the triggering process in each of these 24 *gotts*. During this triggering process, facilitators will use participatory tools, such as transect walk, sanitation mapping, and calculating feces deposition to help community members realize the health effects of open defecation practices in their *gotts*. In the process, basic human emotions, including shame and disgust, will be aroused among the *gott* members regarding their own defecation practices. Successfully implemented, the triggering activities of the CLTS, which normally take half a day for each *gott*, can be a very effective tool to motivate community members to stop open defecation and to eventually construct and use latrines of their own accord.

In accordance with the core principle of CLTS, no material or financial subsidies will be provided for the construction of individual household latrines. Household members will take responsibility for the whole process of latrine construction including (1) pit-hole digging; (2) constructing a slab and pit-hole cover; (3) constructing the walls, door, and roof; and (4) installing hand-washing facilities. The community member’s labor cost for construction of a latrine is expected to be approximately US$5.95 (125 Ethiopian birr as of October 23, 2015) per household. Ten full days of labor are estimated to be required for the construction of an improved latrine per household if two adults were to work together for the procurement of materials (wood, thatch, stone, and so on) and construction of the latrines.

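### Refusing households are replaced by an unspecified neighbour rather than from the existing household list, which leaves the choice of substitute discretionary, apparently after allocation

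*Protocol article*

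**What the plan says.** The Household sampling methods section of the Protocol article describes a sound frame and a sound first draw. It reports that "Supervisors required 8 days to produce a complete household list for all 48" gotts, and that "the survey team leader randomly sampled 25 households from each" gott, using statistical software. Enumerators then visit: "Enumerators will recruit the youngest child under five from each household, from the fifth week of October through the second week of November 2015". When a caregiver is absent, "the enumerator will revisit the same household two more times".

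For refusals the section leaves the list behind. The condition is "If the mother or caregiver refused to be registered", and the consequence is that "a neighboring household with a child under 5 was visited to replace the household". It gives no order, distance, direction or list number to identify the neighbour, and it does not say who makes the choice. Enumerators are the only staff named for the recruitment visits.

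On timing, the CLTS implementation section says that 24 gotts "were selected (intervention arm) and will receive the CLTS intervention". The Eligibility criteria and randomization section describes the stratification by kebelle and the buffer zones in the past tense. The Trial status section says that recruitment had not begun on October 23, 2015. The Study design section starts the latrine intervention in November 2015.

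**The concern.** A random sample from a complete list keeps field staff out of the choice of children. Replacement by an unspecified neighbour lets that choice back in for every refusal. This would be harmless to the comparison if substitutes were chosen in the same way in both arms. That cannot be taken for granted when the arm of a gott may be known at the visit: a substitute might be chosen, for example, because the household looks cooperative or has better hygiene, and to a different degree in the two arms.

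Randomising gotts does not protect against this, because the selection takes place inside gotts after they are allocated. The cohort is closed, so a substitute child stays in it for all survey rounds and for the calendar. The primary endpoint is 7-day diarrhoea reported by a parent, so the type of caregiver enrolled bears directly on it. What is at stake is a possible bias in the between-arm difference in prevalence that a rule of one sentence would prevent.

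**Working it through.** **1. Is the choice of substitute discretionary?** The list exists and is complete, and the first 25 households come from it at random. The replacement rule refers to proximity only. A household usually has more than one neighbour, so the rule does not determine the substitute. This is a rule that the article states, not a detail that it leaves out.

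**2. Could the choice be related to arm?** Set the dates side by side. The 24 intervention gotts are reported as already selected. Recruitment had not started on October 23, 2015, and runs to the second week of November. The latrine intervention begins in November 2015, so the two may overlap. No section says that enumerators or households are unaware of the arm. Allocation before recruitment is therefore a fair inference, and knowledge of the arm is possible but not stated.

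**3. The plan's yardstick.** From the Sample size calculation section: control prevalence p0 = 0.24; 30 % relative reduction, so p1 = 0.24 x 0.70 = 0.168 and the planned difference is 0.072, or 7.2 points; coefficient of variation k = 0.15; 80 % power. The household sample gives m = 25 per gott. Two-sided 5 % is assumed, from the 1.96 in the incidence formula. With the cluster formula of the type printed there, adapted to proportions:

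c = 1 + (1.96 + 0.8416)² x [p0(1-p0)/m + p1(1-p1)/m + k²(p0² + p1²)] / (p0 - p1)²

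= 1 + 7.849 x [0.007296 + 0.005591 + 0.001931] / 0.005184 = 23.44.

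This rounds up to 24 gotts per arm, hence 24 x 25 = 600 children per arm, as the plan states.

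**4. Size of the bias.** Let r be the share of households replaced and d the difference in 7-day prevalence between the substitutes actually taken and those a random draw would have given, in one arm only. An equal d and r in both arms would cancel from the difference under no effect. Then bias = r x d. The documents give neither r nor d, so both are assumptions.

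| Assumed r | Children per arm | Assumed d | Bias | Share of 7.2 points |
|---|---|---|---|---|
| 5 % | 30 of 600 | 5 points | 0.05 x 5 = 0.25 points | 3.5 % |
| 10 % | 60 of 600 | 10 points | 0.10 x 10 = 1.0 point | 13.9 % |

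**5. Against sampling error.** If the design has its stated power, the implied standard error of the difference is about 7.2 / 2.8 = 2.6 points. The bias is then 0.25 / 2.6 = 0.1 to 1.0 / 2.6 = 0.4 standard errors.

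**6. Cross-check on the ratio scale.** If the substitutes in the intervention arm have RR times the prevalence of the others, a true ratio of 1 becomes 1 - r(1 - RR).

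- RR = 0.7: 0.985 with 5 % replaced, 0.97 with 10 %, 0.94 with 20 %.
- RR = 1.25: 1.025 with 10 % replaced, 1.05 with 20 %.
- A true ratio of 0.70, with RR = 0.7: 0.679 with 10 % replaced, 0.658 with 20 %.

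The bias can go in either direction and grows in proportion to the share replaced.

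**The case against.** The strongest reply is that this is small and partly inferred. The sentence is passive: it does not say that the enumerator picks the neighbour, nor does it exclude that the neighbour is taken from the list. No section says that the arm is known at the visit. Discretion arises only after a refusal. Arms are balanced within kebelle, and the October 2015 survey round with its demographic and socioeconomic questionnaire would show a gross imbalance. The upper end of the range needs one household in ten replaced and a gap of 10 points, which is 10 / 24 = 42 % of the control prevalence, in one arm only. All of this stands, and it limits the point to a possibility of modest size. It does not supply a rule for which neighbour is visited.

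Four stronger readings are tempting and are not supported:

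- **Enrolment brings the sanitation campaign in intervention gotts, so refusal must differ by arm.** The Study design and CLTS implementation sections deliver the campaign to the whole gott, and the Sanitation mapping section registers all households in all 48 gotts. The calendar goes to registered households in both arms. Joining the cohort neither brings nor avoids the campaign.
- **Neighbours of sampled households make gotts materially more homogeneous.** The documents give nothing with which to quantify this. At the assumed rates it concerns 1.25 to 2.5 of 25 households per gott.
- **The absence rule is defective because it stops after the revisits.** That is detail which a condensed article may leave to the full protocol.
- **A reserve list would remove recruitment bias altogether.** It removes discretion over the substitute. If refusal itself differs by arm, the refusers are still lost unequally.

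**Conclusion.** The point holds in a limited form. The article states a replacement rule that abandons its own complete list and does not determine the substitute. Because allocation appears to come first and unawareness of the arm is nowhere stated, the choice is open to arm-related selection. The documents do not show that such selection occurs.

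Confidence is high that the rule is loose and lower that it would act differently by arm. The size cannot be determined without a refusal rate. Under the assumptions shown, the bias is a small fraction of the planned difference and well within one standard error, and it would be negligible if refusals are rare. It is worth correcting because the correction is nearly free, not because it threatens the trial. The number of gotts and children does not change.

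**What to change.** Replace the neighbour rule with this: in the same software run that draws the sample, put all listed households of each gott in random order. The first 25 are the sample and the rest form a numbered reserve. A refusal is replaced only by the next reserve number, which the team leader releases. The size stays at 25 per gott and 600 per arm.

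Because the reserve does not deal with refusal that differs by arm, also flag each replacement household in the data, report refusals and replacements by arm, and repeat the primary analysis without replacement households as a sensitivity analysis. At 5-10 % replaced, that analysis keeps 540-570 of 600 children per arm.

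If recruitment has already been completed under the neighbour rule, the flagging, the reporting by arm and the sensitivity analysis can still be done wherever replacements were recorded.

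The cost is a few sentences in the protocol, a printed reserve list, and slightly longer walks for enumerators.
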